Strenuous exercise compared with moderate (Tremblay, et al., 1994; Trapp, et al, 2008) appears to show greater weight loss in some but not all (Jakicic et al. 2003; Tjonna, et al, 2008) studies. Therefore, most people believe that moderate exercise and reduce sedentary activities should be encouraged as a better alternative to increase the daily energy expenditure and to reduce body weight (Westerterp & Plasqui, 2004), mainly because of obese individuals feel more comfort and confidence with the practice of moderate exercise (Piana, et al., 2013). However, few studies have also evaluated the effect of different intensities of exercise on daily energy expenditure in children with overweight.

1. **Objective**

To evaluate the effect of two intensities of exercise on the subsequent spontaneous physical activity energy expenditure among overweight adolescent.

1. **Method**
   1. **Study design**

This is an experimental crossover design, where all selected subjects will undergo three experimental conditions.

All adolescentes enro lled in the 6th and 7th grade in a public school in Niterói, Rio de Janeiro were invited to undergo anthropometric measurements to determine de body mass index (BMI). Only those adolescents classified as overweight according to World Health Organization parameters for age and sex (de Onis, et al., 2007) were included in the study. In order to minimize the risk of stigmatization, eutrophic adolescents will be invite to participate in exercise sessions, with the amount corresponding to 20% of the sample size.

The adolescents will be assessed in five visits. During the first visit, anthropometric measures will be collected. During the second visit, the adolescents will undergo a maximum field test to evaluate aerobic capacity (Leger, et al., 1988). At the end of the test, the maximum heart rate will be determined and the heart rate zone for each experimental session will be calculated. The third and fourth visits will be experimental sessions with different training intensities and the fifth session will be the control session (no exercise), interspersed by a period of one week.(**figure 2**).

[figure not shown]

**Figure 2.** Scheme of the experimental sessions

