The experimental sessions will be structured in two phases: warm-up, training, cool-down. The exercise protocol is different between the experimental sessions (moderate and vigorous) only in the training phase, with similar warm-up and cool-down phases in both sessions. During the warm-up, subjects will be instructed to start walking at a low-intensity, and then increase their pace until they reached values close to 64% of maximum heart rate. In the cool-down phase, adolescents will be instructed to gradually reduce their pace in order to reach heart rate values close to those found at rest. (**figure 3**).

[figure not shown]

**Figure 3.** Warm-up and cool-down characteristics

The main part of the moderate session (MS) consist of 4 sets of 10 minutes walking at moderate intensity (64% to 76% of maximum heart rate), interspersed with 5 minutes of light walking (below 64% of maximum heart rate) for recovery between sets. (**figure 4**).

[figure not shown]

**Figure 4.** Main part of the moderate session

The main part of vigorous session (VS) consist on 4 sets of 10 minutes running at vigorous intensity (77% to 95% of maximum heart rate), interspersed with 5 minutes of light walking (below 64% of maximum heart rate) for the recovery between sets. (**figure 5**).

[figure not shown]

**Figure 5.** Main part of the vigorous session

During the two experimental sessions, the adolescents will be supervised by a trained exercise physiologist to ensure that they will perform the intervention protocol properly. The target heart rate will be monitored using heart rate monitors. One week was defined as a washout period (**figure 2**).

During the exercise sessions and for a period of six days, energy expenditure and the amount of physical activity will be evaluated through accelerometers. It consists of a small device that is placed at the hip region and should be removed only during bathing or during the practice of aquatic activities. The use of this device is considered safe, however, for an extended period, may cause discomfort. The adolescents will be informed not to perform physical exercises in the three days before each session, and not drinking alcohol, coffee or any other stimulant in the 24 hours prior to each session.

- 1. **Sample size**

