- - 1. **Energy expenditure measurements**

The physical activity energy expenditure during one week will be assessed through Actigraph accelerometers, wGT3X-BT model. It is a portable, lightweight and non-invasive device, providing an objective measurement of physical activity. The accelerometer will be placed on the day before each experimental session, at the same time and removed after one week.

This device is often used in epidemiological studies to evaluate the recommendations of physical activity for children and adolescents, as well as providing an estimate of energy expenditure derived from the activities. In order to proceed with the evaluations, threshold values ​​were developed to fractionate the intensity into categories: sedentary, light, moderate and intense.

The border points that will be used for each intensity range have been proposed by Evenson (2008), which below 100 counts per minute, physical activity is classified as sedentary between, 100 and 2296 counts per minute as light activity, between 2296 and 4012 as moderate and above 4012 vigorous physical activity. These points have shown greater precision to classify physical activity intensity than other points established in other studies (Trost, et al., 2011).

The sampling period (epoch) in this study is 5 seconds to capture the possibility of minor variations in movements performed by adolescents (Trost, et al., 2005). Days with less than 600 minutes of recorded data or more than 60 minutes counts of consecutive zeros, will be excluded from the analysis (Choi et al., 2011).

Adolescents will be instructed not to take out the device during that time, except for the period of the bath and while practicing water activities.

- 1. **Data analysis**

The descriptive analyses will calculate the mean and standard deviations for continuous and percentages for categorical variables. Differences in daily and accumulated energy expenditure between exercise sessions will be performed using linear mixed models, which takes into account the correlations between repeated measures over time.

The analysis will be performed in SAS 9.3 software (Statistical Analysis System, USA) and statistical significance set at p<0.05 for all analyses.

•

•

•

•

1. **References**

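### One run of more than 60 minutes of zero counts excludes the whole accelerometer day, although the device is worn day and night and no removal of sleep is stated

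*Protocol*

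**What the plan says.** The rule stands in the Protocol under Energy expenditure measurements: "Days with less than 600 minutes of recorded data or more than 60 minutes counts of consecutive zeros, will be excluded from the analysis". Either criterion is enough, and what is excluded is the day.

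The same section sets the wear instruction: "Adolescents will be instructed not to take out the device during that time, except for the period of the bath and while practicing water activities". Study design agrees that the device "should be removed only during bathing or during the practice of aquatic activities". Neither place exempts sleep, and no section says that night hours are cut out before the rule is applied.

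Three other statements bear on the point:

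- Intensity is classed so that "below 100 counts per minute, physical activity is classified as sedentary".
- Study design sets the measurement period: "During the exercise sessions and for a period of six days, energy expenditure and the amount of physical activity will be evaluated through accelerometers".
- The Objective is "To evaluate the effect of two intensities of exercise on the subsequent spontaneous physical activity energy expenditure among overweight adolescent".

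Data analysis plans linear mixed models for daily and for accumulated energy expenditure.

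**The concern.** A long run of zeros is normally a sign that the device was off, or the wearer motionless, for that stretch. Here it disqualifies the rest of the day as well. Three consequences follow.

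- **Sleep.** A participant who follows the wear instruction records the night. Any night with more than an hour without a registered count fails the day, however good the waking record.
- **Waking time.** If sleep is removed first, a long rest still deletes the day. So does a permitted removal of more than an hour for swimming.
- **Selection on the outcome.** The trial asks whether adolescents move less after exercise, and prolonged stillness is one form of moving less. A rule that deletes days for stillness can therefore delete more days in the condition where compensation occurs. The mixed model allows for correlation between repeated measures, but that does not by itself correct deletion that depends on the deleted day's own value.

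Accumulated expenditure is affected too, because each deleted day leaves a gap in the six-day total.

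**Working it through.** **The plan's own figure.** The Protocol gives no expected number of valid days. The only figure to reproduce is the sample size of 27. With a difference of 110 kcal, an SD of 110 kcal taken as within-subject, two-sided α 0.05 (sidedness assumed) and power 0.90:

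n = 2 × (1.960 + 1.282)² × 110² / 110² = 21.01, rounded up to 22.

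For 20% refusal, 21.01 / 0.8 = 26.3, rounded up to 27; also 22 × 1.2 = 26.4, rounded up to 27. The figure reproduces. The allowance is for refusals only, with none for lost days.

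**Which days the rule removes.** Under round-the-clock wear a day has 1,440 minutes.

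- With 7 to 9 hours of sleep removed, 1,440 − 420 = 1,020 to 1,440 − 540 = 900 minutes remain. Both pass the 600-minute test, but the written rule drops the day if the night holds one zero run above 60 minutes.
- With 61 minutes of swimming, 1,440 − 61 = 1,379 minutes are recorded on the body, or 839 to 959 after removing 9 or 7 hours of sleep. The written rule drops this day too.

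**Loss from sleep alone.** The documents give no rate of zero runs, so the rate is assumed. Registered movements in sleep are taken as a Poisson process at λ per hour over H = 7, 8 or 9 hours. A day is lost if the longest gap exceeds 1 hour. Simulated shares of days lost (20,000 nights each; an exact calculation agrees within one percentage point):

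| Movements per hour | Days lost, H = 7 to 9 |
|---|---|
| 1 | over 99% |
| 2 | 92-97% |
| 3 | 67-77% |
| 4 | 39-47% |
| 6 | 9-12% |
| 8 | about 2% |

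With daily loss p and independent nights, the chance that a child has at least one valid day in each of three six-day periods is (1 − p⁶)³. For H = 8:

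- λ = 2, p = 0.948: 6 × 0.052 = 0.3 days kept per period; (1 − 0.726)³ = 0.02, or about 0.5 of 22 children.
- λ = 3, p = 0.725: 1.65 days kept; (1 − 0.145)³ = 0.62, or 13.7 of 22.
- λ = 4, p = 0.427: 3.4 days kept; 0.98, or 21.6 of 22.

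**Selective loss.** The true fall is set at 110 kcal and the day-to-day SD at 110 kcal, both borrowed from Sample size. The log-odds of losing a day rise by b for each SD of lower expenditure. The loss probability at the control mean is 20%, 40% or 60%. The dependence b is assumed.

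| b | Observed fall (kcal) | Attenuation |
|---|---|---|
| 0 | 110 | 0% |
| 0.5 | 104-106 | 4-5% |
| 1.0 | 91-94 | 15-17% |
| 1.5 | 77-82 | 25-30% |

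Attenuation is (110 − observed) / 110. At b = 1.0 and 40%, the condition with the fall loses 62% of days against 42% in the other. These are comparisons of pooled independent days, not of the planned mixed model.

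**The case against.** The strongest reply is that the sentence is loosely worded. A 600-minute minimum does little under 24-hour recording unless some time is taken out first, so the authors may have meant to strip zero periods as non-wear and then count what is left. Sleep windows and software settings are also often left to an analysis plan or a processing manual. The reading is possible, but it is not what the sentence says, and an analyst who follows the text would discard the day. Nor does removing sleep rescue the waking cases above.

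Two stronger readings are tempting, and the objection is right to resist both.

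- A reader might infer that almost no data would survive. That needs about two or fewer registered movements per hour of sleep and no prior removal of sleep. The documents give no such rate, and at 8 per hour the loss is about 2%.
- A reader might infer that the rule demonstrably biases the trial towards no compensation. The size of the attenuation comes from an assumed dependence and is zero without it. A day's longest zero run is not the same thing as its energy expenditure. Days lost to swimming are active days, and losing them may act in the opposite direction.

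It also stands that dropping days with much non-wear is a defensible complete-day choice. Keeping them has a cost, because wear time then differs between days.

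**Conclusion.** The point holds as a badly fixed data rule for the main outcome. The Protocol makes the day the unit of exclusion and prescribes wear that includes sleep, with no step between the two. Followed exactly, the rule can discard days that are complete by the 600-minute standard.

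The amount is uncertain: from a few percent of days to nearly all through sleep, depending wholly on the assumed movement rate. An effect on the estimate is possible, illustratively 0% to about 30% of a 110 kcal fall where waking stillness drives deletion. With swimming days acting the other way, the net direction is not established. The case for changing the rule rests on the conflict in the text and on the link between stillness and the outcome, not on any one of these percentages.

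**What to change.** Replace the sentence with a rule in three steps:

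1. Runs of more than 60 minutes of consecutive zeros are removed as non-wear intervals and are not a reason to exclude the day.
2. Sleep time is identified and removed by one named rule, applied identically in all three conditions.
3. A day is kept if at least 600 minutes of waking wear remain.

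Because retained days will differ in wear time, adjust daily energy expenditure for wear minutes or express it per wear hour. Report valid days and wear time by condition.

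The cost is a short amendment, a setting in the accelerometer processing and the choice of a sleep rule, which the Protocol does not yet name. There is a small downside: unrecorded water activity is understated on retained days, and true waking stillness of over an hour is still treated as non-wear. The rest of the day is kept.

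### The objective concerns spontaneous activity after the session, but the stated analysis is of daily and accumulated expenditure, with no rule removing the session's own energy and no named contrast with control

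*Protocol*

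**What the plan says.** The Objective section states one aim: "To evaluate the effect of two intensities of exercise on the subsequent spontaneous physical activity energy expenditure among overweight adolescent".

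Under Study design, "This is an experimental crossover design, where all selected subjects will undergo three experimental conditions". Two are exercise sessions, each with four 10-minute sets, walked in the moderate session and run in the vigorous one. The third is the control: "the fifth session will be the control session (no exercise), interspersed by a period of one week".

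On measurement, Study design says: "During the exercise sessions and for a period of six days, energy expenditure and the amount of physical activity will be evaluated through accelerometers". The section on energy expenditure measurements adds: "The accelerometer will be placed on the day before each experimental session, at the same time and removed after one week". Data are stored in 5-second epochs.

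The Data analysis section names one inferential comparison: "Differences in daily and accumulated energy expenditure between exercise sessions will be performed using linear mixed models". The Sample size section also works from daily energy expenditure, with a difference between sessions of 110 kcal and a standard deviation of 110 kcal.

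The protocol nowhere says whether the minutes of supervised exercise enter the analysed values, and nowhere states a comparison with control.

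**The concern.** The objective contains two restrictions: the activity must be spontaneous, and it must come after the session. Supervised walking or running at a set heart rate is neither. The analysed quantity, as worded, carries neither restriction.

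This matters because the two components pull in opposite directions. A harder session raises that day's expenditure by design, while compensation lowers what follows. In a sum they offset each other. Full compensation after vigorous exercise would appear as no difference in the accumulated total, and no compensation at all would appear as a higher total after vigorous exercise. The protocol's own background describes the first pattern: in a training study of healthy elderly people, total expenditure did not change because spontaneous activity fell. It also cites an adult study that compared days with and without exercise after taking the workout out.

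The control has a similar role. If both intensities led to the same fall in later activity, a vigorous-versus-moderate comparison would show nothing. Only a comparison with the no-exercise condition would reveal it.

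**Working it through.** **1. The plan's own figure.** Inputs from the Sample size section: difference 110 kcal, SD 110 kcal, α 0.05 (taken as two-sided), β 0.10, refusal 20%.

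- n = 2 × (1.960 + 1.282)² × (110/110)² = 21.01, rounded up to 22. This is the crossover total if 110 kcal is the within-subject SD.
- Refusal allowance: 21.01/0.8 = 26.3, giving 27; or 22 × 1.2 = 26.4, giving 27. (22/0.8 = 27.5 would give 28.)

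The stated 27 is reproduced, but for daily expenditure. The documents give no SD for expenditure after the session, so no corresponding number can be computed for that outcome.

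**2. Objective and analysis side by side.**

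| Element | Objective | Stated analysis |
|---|---|---|
| Quantity | Expenditure on spontaneous activity | Daily and accumulated expenditure |
| Time | After the session | Recording covers the session and six days |
| Session energy | Excluded by meaning | No exclusion stated |
| Comparison | Effect of two intensities | Between exercise sessions; control not named |

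**3. Size of the prescribed difference.** The protocol gives the duration (4 × 10 = 40 minutes in each session) but no body weights or energy costs. Assumed: 50 to 65 kg, walking 3.5 to 4.5 METs, running 7 to 9 METs. Warm-up, cool-down and recovery walks are alike in both sessions and cancel between them.

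Net cost = (METs − 1) × kg × 40/60.

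- Moderate: 2.5 × 50 × 2/3 = 83 kcal to 3.5 × 65 × 2/3 = 152 kcal.
- Vigorous: 6 × 50 × 2/3 = 200 kcal to 8 × 65 × 2/3 = 347 kcal.

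Vigorous minus moderate, S = (running METs − walking METs) × kg × 40/60:

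- Lowest: (7 − 4.5) × 50 × 2/3 = 83 kcal.
- Middle: (8 − 4) × 55 × 2/3 = 147 kcal.
- Highest: (9 − 3.5) × 65 × 2/3 = 238 kcal.

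**4. What each outcome would show.** Let c be the fraction of S that is later compensated. The accumulated difference is S(1 − c) and the subsequent difference is −cS.

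| c | Accumulated difference (kcal) | Subsequent difference (kcal) |
|---|---|---|
| 0 | +83 to +238 | 0 |
| 0.5 | +42 to +119 | −42 to −119 |
| 1 | 0 | −83 to −238 |

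The accumulated total is furthest from zero when there is nothing to find for the objective, and zero when compensation is complete.

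**5. Where the problem stops.** A day after the session day contains no prescribed exercise, so differences on those days reflect subsequent activity directly. Averaged over seven days (session day plus six), S adds 83/7 = 12 to 238/7 = 34 kcal per day.

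**The case against.** Several points on the other side have weight.

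- **Inclusion of session energy is inferred.** The protocol says when the device records, not which epochs enter the model. A reader might infer that the session and the day before it are analysed; the text does not say so. Epoch selection is often left to a statistical analysis plan, which may exist. This stands as a limit on the claim. It does not remove the mismatch, because the quantity named in the analysis differs from the one in the objective.
- **Later days are informative.** A reader might infer that the analysis cannot test the objective at all. The documents do not support that: the mixed model covers daily values as repeated measures, and those after the session day bear on the question. The point is confined to the session day and the accumulated total. The session day still matters, since it holds the hours immediately after exercise.
- **Control may be in the model.** The protocol calls the control a session, and the Sample size section speaks simply of sessions. A reader might infer that control is excluded; nothing says that. Against this, the section on the shuttle run test glosses exercise session as moderate and vigorous. It is an ambiguity about a comparison that should be explicit.
- **The built-in difference need not exceed 110 kcal.** At the low end of the assumed range it is 83 kcal. It is also a one-off cost, and spread over the week it is well below 110 kcal per day. The weights and METs are assumptions, and an accelerometer estimate may differ from a MET-based cost.
- **Daily expenditure is a legitimate outcome.** It is in the project title and the sample size, and the background says total expenditure should be the focus for weight reduction. That is a good reason to keep reporting it, but it is not what the Objective section asks.

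**Conclusion.** The concern holds within limits. The stated objective and the stated analysis name different quantities. As written, the session-day value and the accumulated total can combine prescribed exercise with compensation of the opposite sign, and so cannot isolate subsequent spontaneous activity. The prescribed vigorous-minus-moderate difference is about 83 to 238 kcal under the assumed weights and METs, of the same order as the 110 kcal planning difference but not above it throughout. Daily values on later days are unaffected and do inform the objective. The missing control contrast is an ambiguity and should not be read as an exclusion. The conclusion about the total rests on reading the recording window as the analysis window, which is the plain reading in the absence of any stated exclusion.

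**What to change.** In the Data analysis section:

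1. Define the outcome for the objective as physical activity energy expenditure from the end of the session to the end of the recording window, leaving out the session interval and the day before the session. In the control condition, drop the same clock interval so that the windows match.
2. State that the mixed model includes all three conditions, and name the contrasts: moderate versus control, vigorous versus control, and vigorous versus moderate.
3. Keep total daily and accumulated expenditure, session included, as an additional reported outcome.
4. In the Sample size section, say that the 110 kcal difference and SD of 110 kcal refer to daily expenditure and that the 27 was not derived for the post-session outcome.

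The cost is small. The 5-second epochs allow the split without new measurement, provided session start and end times are logged for each participant. The one real downside is that the post-session outcome has no power calculation behind it, and the documents give no SD from which to make one.

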Sample size was calculated based on a mean difference in daily energy expenditure between sessions of 110 kcal (Wang, et al., 2006) with a coefficient of variation equal to 1 (standard deviation of 110 kcal) (van Belle, 2008). The sample size required for the study, with an α of 0.05 and β of 0.10 and estimating a refusal rate of 20%, was 27 children (Julious, 2009).

- 1. **Measurement procedures**
     1. **Anthropometric measurements**

Body weight will be measured using a portable electronic scale (Tanita BC -558 Japan) with a capacity of 150 kg and precision of 50g, while wearing light clothes and no shoes. Height will be measured using a portable stadiometer (Alturexata, Brazil) with an amplitude of 200 cm and variation of 0.1 cm. Participants will be instructed to remain without shoes, feet together and keeping the head in the Frankfurt plane (Madsen, et al., 2008). Two measurements will be made and considered the mean values ​​for analysis. The classification of nutritional status will be based on BMI (kg/m2) cutoff points recommended by the World Health Organization (de Onis, et al., 2007).

- - 1. **Shuttle run test**

Cardiorespiratory fitness will be assessed by a maximum field test, specific to the age of the study group. The shuttle run, is a valid test (Leger et al., 1988) and widely used in studies with adolescents worldwide (Jimenez-Pavon et al ., 2013; veses, et al, 2014). The purpose of this test is to estimate the maximum oxygen consumption. It is a progressive, maximum and indirect test. Participants are placed at the starting line and begin the test with the first beep. They must arrive at the marked location, bypassing the line, before sounding the next beep. The direction changes must be made to stop and start the other way, avoiding curvilinear paths. Every minute, the time between beeps will decrease, which mean an increase in the speed. The test will be completed with the participant's withdrawal, or when it fails to reach the scored line two consecutive times. A doctor will be present during the test for possible complications. Each participant will use a heart rate monitor during the test and the maximum heart rate will be recorded. Thus, the intensity of each exercise session (moderate and vigorous) will be calculated, individually, according to the percentage of the maximum frequency established for moderate and vigorous intensity (Physical Activity Guidelines Advisory Committee, 2008).

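### One 0.05 threshold covers daily and accumulated energy expenditure across three sessions, but no deciding outcome or contrast is named, so the false-positive rate depends on which tests are run

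*Protocol*

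**What the plan says.** Four parts of the protocol bear on this.

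- **Study design:** "all selected subjects will undergo three experimental conditions", namely moderate exercise, vigorous exercise and a control session without exercise. On the recording period: "During the exercise sessions and for a period of six days, energy expenditure and the amount of physical activity will be evaluated through accelerometers".
- **Sample size:** the calculation uses a "mean difference in daily energy expenditure between sessions of 110 kcal", a "standard deviation of 110 kcal", and error rates "with an α of 0.05 and β of 0.10". It does not say which two sessions.
- **Data analysis:** "Differences in daily and accumulated energy expenditure between exercise sessions will be performed using linear mixed models", allowing for correlation between repeated measures, and "statistical significance set at p<0.05 for all analyses".
- **Objective:** it concerns how two exercise intensities affect later spontaneous activity energy expenditure. It names neither a contrast nor a time window.

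No section designates a primary outcome, a primary contrast, an order of testing or an exploratory tier.

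**The concern.** Three conditions give three possible pairs. Energy expenditure is to be examined in a daily and an accumulated form over about a week. The only decision rule in the document is the common 0.05 threshold, and nothing says which result answers the objective.

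The candidate comparisons ask different questions and can disagree. Vigorous may differ from moderate while neither differs from control, or a single day may dip while the total does not. The protocol's own background describes the evidence on compensation after exercise as contradictory. A positive finding picked from several unranked tests would do little to settle that, because its error rate could be well above the nominal 5%.

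**Working it through.** **Step 1. Reproduce the sample size, to see how many comparisons it allows for.** Inputs from Sample size: difference 110 kcal, SD 110 kcal, alpha 0.05, beta 0.10, refusal 20%.

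- Two-sided alpha: n = 2 × (1.960 + 1.282)² × (110/110)² = 21.01. Then 21.01/0.8 = 26.3, which rounds up to the stated 27.
- One-sided alpha: 2 × (1.645 + 1.282)² / 0.8 = 21.4, so 22. This does not match.
- 110 kcal taken as the SD of paired differences: (1.960 + 1.282)² = 10.5, rounded up to 11, and 11/0.8 = 13.75, so 14. This does not match.

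The stated 27 is thus the size for one unadjusted two-sided comparison at 0.05.

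**Step 2. Count the tests that the text permits.**

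- Moderate versus vigorous, once per outcome form: 2 tests.
- All three pairs on one outcome: 3 tests.
- Moderate versus vigorous on each day and the total: 6 + 1 = 7, or 7 + 1 = 8.
- All pairs on each day and the total: 3 × 6 + 3 = 21, or 3 × 7 + 3 = 24.

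Six days is the figure in Study design. Seven applies if the session day is counted separately, which is an assumption.

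**Step 3. Chance of at least one p<0.05 when there is no effect.** For k independent tests it is 1 − 0.95^k, so 0.0975 for k = 2 and 0.143 for k = 3. The tests here are correlated, so they were simulated: 20,000 null trials per setting, n = 22 and 27, two-sided paired t-tests. The between-day correlation of session deviations was set at 0, 0.3, 0.5 and 0.8. The protocol gives no value, so this range is assumed.

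| Tests at 0.05 | Chance of at least one false positive |
| --- | --- |
| Moderate vs vigorous, one summary outcome | 5.1% |
| Moderate vs vigorous, daily and accumulated once each | 5% if the two coincide, 9.75% if independent |
| Three pairs, one summary outcome, no overall test first | 12.3% to 12.5% |
| Three pairs, one summary outcome, only after a significant 2-df session test | 4.9% |
| Moderate vs vigorous, each of 6 or 7 days plus total | 14% (correlation 0.8) to 32% (correlation 0) |
| Three pairs, each of 6 or 7 days plus total | 31% (correlation 0.8) to 63% (correlation 0) |

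For n = 27 and six days, the moderate versus vigorous rates at correlations 0, 0.3, 0.5 and 0.8 are 28.7%, 25.3%, 21.7% and 14.0%. With all three pairs they are 57.0%, 52.1%, 45.6% and 31.4%.

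Paired t-tests stand in for contrasts from the planned mixed model, so the figures are approximations to it.

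**The case against.** The strongest reply is that the protocol does not say that all three pairs are compared or that each day is tested separately. The analysis is of differences between exercise sessions, and the control session is described as having no exercise, so moderate versus vigorous may be the only pair meant. A mixed model can give one session effect pooled over days. If daily means the average per day and accumulated the sum over the same days, the two tests nearly coincide. On these readings the error rate stays between about 5% and 10%.

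A significance threshold also does not say unadjusted. It is compatible with a fixed sequence or an overall test first, and a statistical analysis plan that is not shown could supply either.

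Much of this stands. A reader might infer that the protocol commits to about 21 unadjusted tests, that 12% is the least possible error rate, or that more than half of null trials would show a false intensity effect. The documents support none of these:

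- The count of 21 needs every pair on every day.
- Rates above 50% also need weakly correlated days.
- Some permitted readings keep 5%.
- A false contrast with control is a false session effect, not strictly an intensity effect.

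What the reply does not remove is that the deciding outcome and contrast belong in the protocol, because the sample size depends on them. The Sample size section leaves the pair open, and Data analysis puts two outcome forms on an equal footing. Day-by-day comparison is a natural reading of daily expenditure with repeated measures. On that reading, even moderate versus vigorous alone reaches 14% to 32%.

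**Conclusion.** The point holds in a conditional form. The protocol fixes a threshold for all analyses but not which analysis decides the trial, so the overall false-positive rate is undefined. Depending on the reading, it runs from about 5% to roughly 60%.

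The lower figures assume one contrast tested once per outcome, or an overall session test used as a gate. The higher ones assume separate daily tests without a gate, and they rest on an assumed between-day correlation of 0 to 0.8.

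This does not show that the trial will exceed 5%. It shows that the text does not prevent it, although the sample size was set for one comparison at 5%. The point is worth correcting before analysis because the correction costs almost nothing.

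**What to change.** In Data analysis, state the following.

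1. **Primary outcome:** mean daily physical activity energy expenditure over the days after the session, with those days defined. This stays on the per-day scale of the sample size. An accumulated total would not, and its power would depend on between-day correlation and on how long any effect lasts, neither of which is given.
2. **Primary contrast:** vigorous versus moderate, two-sided 0.05, which matches the two intensities in the objective.
3. **Contrasts with control:** tested in a stated fixed order, each only if the one before it is significant. If all three pairs matter equally, test the 2-df session effect in the mixed model at 0.05 first, and the pairs at 0.05 only if it is significant. With three conditions this is a closed test and holds 5% for that outcome: once one condition differs from the others, at most one pair can still be truly equal.
4. **Accumulated and day-by-day comparisons:** secondary or exploratory, given as estimates with 95% confidence intervals.

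The cost is a few sentences, with no new data. The primary test keeps two-sided 0.05, so the change in testing rules does not alter the 27. The protocol does not say whether its SD of 110 kcal refers to a single day or to a mean over days, and the sponsor should confirm this. The small downside is that an isolated significant day, or a control contrast later in the order, can no longer be claimed as confirmatory.
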